### Statistical methods

The Shapiro–Wilk test will be used to test the normality of the data and Levene’s test for the homogeneity of variances. When data will be normally distributed and the assumption of homogeneity will be not violated, parametric analyses will be computed. When one assumption will be not meet, non-parametric tests will be conducted or a log-transformation of distribution will be applied, if appropriate.

The groups will be compared on demographic and categorical variables using Chi-Square analyses. The primary outcome (EDRC score of EDI-3) will be included in a General Linear Model and will be analyzed by means of repeated measures ANOVA with Group (active tDCS + TAU vs sham tDCS + TAU) as between-factor and Follow-ups (T0-T1 vs T0-T2 vs T0-T3 vs T0-T4 vs T0-T5) as within-factor. The same analyses will be applied to the secondary psychological outcomes (EAT-26 total score, BUT-GSI, and CBCL 6–18, YSR 11–18, MASC-2 and CDI-2 subscale’s t-scores). Post hoc comparisons will be run by means of Bonferroni test.

For secondary neurophysiological outcomes, the differences between the left and right hemisphere at baseline and between the recordings T0 and T1 will be evaluated on both TEPs component and frequency through a non-parametric cluster based permutation tests to correct for multiple comparisons as developed in the ft_timelockstatistics\ ft_freqstatistics functions in Fieldtrip [74]. The EEG signal will be analyzed for defining a resting state pattern with frequency inspection, using a Fourier analysis. For TMS data, prior to undergoing ANOVA, the normal distribution of data will be assessed by means of the Shapiro-Wilks test. The level of significance was set at 0.05. For the SICI, SAI, and iTBS protocols, we will perform three ANOVAs on the normalized values calculated as the percentage of the mean peak-to-peak amplitude size of the unconditioned TS with GROUP (active vs sham) as the between-subject factor and ISI (for SICI and SAI protocols) or TIME (for iTBS protocol) as within-subject factors. When a significant main effect will be reached, Bonferroni post hoc comparisons will be performed to characterize the specific effect.

For secondary physiological outcomes, differences in saliva CAR, CAR AUCg and AUCi between groups (active tDCS + TAU vs sham tDCS + TAU) will be evaluated by repeated measures ANOVAs with time (T0 vs T1 vs T2 vs T4) as within-subject factors; and differences in BMI between groups (active tDCS + TAU vs sham tDCS + TAU) will be evaluated by repeated measures ANOVAs with time (T0 vs T1 vs T2 vs T3 vs T4 vs T5) as within-subject factors.

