### Outcomes measures

#### Primary outcome measure

We believe that active tDCS, coupled with TAU, will enhance outcome of traditional treatment and will have a substantial impact on symptoms recovery of AN.

The primary end-point of the study is significant improvement on AN psychopathology at T1, assessed as changes in EDI-3 ED-specific (EDRC score).

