### Sample size

The sample size was calculated by a priori analysis in G * Power, version 3.1.9.7 (The G*Power Team, Düsseldorf, Germany).

Assuming a correlation of 0.80 in the primary outcome measure (EDRC score of EDI-3 questionnaire) with an estimated f = 0.08, α value = 0.05 (i.e., probability of false positives of 5%), and β = 0.80 (i.e., at least 80% power), the sample size that was required for repeated-measures analysis of variance (ANOVA) with 2 groups (active tDCS vs sham tDCS) and 6 measurements (T0 vs. T1 vs. T2 vs. T3 vs. T4 vs. T5) was 68 (i.e., 34 per group). Considering a 15% dropout rate in the follow-ups, we will plan to recruit a total of 80 participants (i.e., 40 per group).

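### The primary EDRC test and its effect scale are not fixed: assumption pre-tests on the trial data decide the method, and two unranked fallbacks are left to judgement after the data are seen

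*Protocol article*

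**What the plan says.** All of this is in the protocol article, mostly under Statistical methods.

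- The gate: the Shapiro-Wilk "test will be used to test the normality of the data and Levene’s test for the homogeneity of variances". The planned analysis is conditional on both: "When data will be normally distributed and the assumption of homogeneity will be not violated, parametric analyses will be computed".
- The fallback: "When one assumption will be not meet, non-parametric tests will be conducted or a log-transformation of distribution will be applied, if appropriate".
- The primary model: EDRC is "analyzed by means of repeated measures ANOVA with Group (active tDCS + TAU vs sham tDCS + TAU) as between-factor". Its repeated factor is written with five levels: "Follow-ups (T0-T1 vs T0-T2 vs T0-T3 vs T0-T4 vs T0-T5) as within-factor".
- The primary endpoint (Primary outcome measure): "significant improvement on AN psychopathology at T1, assessed as changes in EDI-3 ED-specific (EDRC score".
- For contrast, BMI is analysed by "repeated measures ANOVAs with time (T0 vs T1 vs T2 vs T3 vs T4 vs T5) as within-subject factors", that is, on raw time points.
- Sample size: "Assuming a correlation of 0.80 in the primary outcome measure", with f = 0.08, alpha 0.05, 80% power, 2 groups and 6 measurements, giving 68 patients, raised to 80 for 15% dropout.

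The gate opens the section and exempts no outcome, so it covers the primary one. The section does not give the level of the pre-tests. Nor does it say whether they are applied to raw scores, changes or residuals, or whether by group or pooled.

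**The concern.** A primary analysis should be identifiable before the data exist. Here the data choose it in two steps. The pre-tests first decide whether the ANOVA is run. If it is not, someone chooses between a log-transformation and a non-parametric test that has no name. These options answer different questions: the ANOVA compares mean differences, a log analysis compares ratios, and a rank test compares orderings. Two analysts following the section faithfully could report different primary results on different scales.

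A second difficulty concerns the primary outcome itself. If its within-factor levels are differences from baseline, a patient who is unchanged or worse has a zero or negative value, and a direct log does not exist for that value.

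**Working it through.** **1. The plan's own figure.** Inputs from Sample size: f = 0.08, correlation ρ = 0.80, m = 6 measurements, k = 2 groups, alpha = 0.05. For the within-between interaction:

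- λ = f²·N·m/(1 − ρ) = 0.0064 × 68 × 6 / 0.20 = 13.06
- df1 = (k − 1)(m − 1) = 5; df2 = (N − k)(m − 1) = 66 × 5 = 330
- Power from the noncentral F = 0.8004, and 68 is the smallest even N that reaches 0.80
- Dropout: 68 / (1 − 0.15) = 80

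Both figures reproduce. The group main effect under the same inputs would need 1,024, so 68 belongs to the parametric interaction test. No power is stated for either fallback.

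**2. How often the gate diverts a trial that meets its assumptions.** Setting: 3,000 simulated trials, 34 per group, multivariate normal, equal variances, ρ = 0.80, each pre-test at an assumed 0.05. The last column is a rough cross-check that treats the tests as independent.

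| How the pre-tests are applied | Tests | Simulated | 1 − 0.95^tests |
|---|---|---|---|
| T1 change only, pooled residuals | 2 | 10% | 10% |
| All five changes, pooled residuals | 10 | 42% | 40% |
| All five changes, per group | 15 | 55% | 54% |

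In the last row, at least one Shapiro-Wilk test rejects in 41% of trials and at least one Levene test in 24%. Separate runs of the T1-only, per-group version (3 tests) gave 14%, which agrees with 1 − 0.95³ = 14%.

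**3. Whether a log can be applied to changes.** Assume equal variance at each visit. The SD of a change, in baseline SDs, is √(2(1 − 0.80)) = 0.632. The share of changes at or below zero is Φ(−d/0.632), where d is the mean improvement. The documents give no value for d, so a range is shown:

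| Assumed d (baseline SD) | 0 | 0.2 | 0.5 | 0.8 | 1.0 |
|---|---|---|---|---|---|
| Share of changes ≤ 0 | 50% | 38% | 21% | 10% | 6% |

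The chance that at least one of 68 patients has such a change is 1 − (1 − share)^68. At d = 1.0 this is 1 − 0.943^68, about 98%, and it is higher for smaller d.

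**4. Effect on type I error.** Null trials were simulated with 34 per arm and ρ = 0.80.

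- Fixed switch from t-test to Mann-Whitney at T1: 4.8% with normal data and 4.8% with skewed data. Another run gave 5.6%, against 5.5% for the t-test used unconditionally.
- Fixed switch from the Group × Follow-ups ANOVA to its rank-transformed version: 5.5% (normal) and 5.4% (skewed).
- After a pre-test rejection, taking the smaller p-value of Mann-Whitney and a log-ratio t-test at T1: 5.7% (normal) to 6.3% (skewed). Another run gave 5.8%.

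With 4,000 trials the Monte Carlo standard error near 5% is √(0.05 × 0.95 / 4,000), about 0.3 percentage points.

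**The case against.** The best defence is that the sentence is a general rule for every outcome, several of which are strictly positive and suit a log. Its closing qualifier lets the analyst decline a log where it does not fit. A condensed article may also leave the name of a fallback test to a document not shown. Much of this stands, and it limits what can be concluded. Four stronger readings are tempting, and the protocol article does not support them.

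- *Both fallbacks fail.* The qualifier does not force a log onto differences. Raw EDRC scores could be logged before differencing if all are positive, although the effect then becomes a ratio. Rank-based and permutation methods for group-by-time designs also exist. The fallbacks are unfixed rather than unusable.
- *The planned analysis would be abandoned about half the time.* That is the upper end of a range which depends on details the section leaves open.
- *The 5% error rate is materially lost.* A fixed switch leaves it near nominal, and even selecting by p-value adds only about one percentage point.
- *Non-responders would be dropped.* Nothing says that undefined logs would be excluded.

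The change-score premise is also a reading. The primary endpoint and the contrast with the BMI model favour it, but Sample size counts six raw measurements.

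The defence does not remove the rule itself. The article states that method selection depends on the data and gives two alternatives without an order. That is a choice written badly, not a detail left out.

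**Conclusion.** The point holds as a defect of specification. The primary EDRC test and its estimand depend on pre-tests of the trial data and on a later judgement between two unranked options. Even when the assumptions are true, the planned ANOVA would be set aside in about 10% to 55% of trials. This rests on a 0.05 pre-test level, 34 per arm and the plan's correlation of 0.80. The log problem is conditional: it arises if the within-factor levels are differences, and its extent (6% to 50% of patients) rests on assumed mean improvements of 1 to 0 baseline SD. Type I inflation is small and is not the reason to act. The plan should be changed because the reported effect could be a difference, a ratio or a rank comparison, and because the sample size supports only the first of these methods.

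**What to change.** - Remove the pre-test gate for the primary outcome.
- Prespecify one EDRC analysis, used whatever the distribution looks like. One suitable choice is a baseline-adjusted mixed model or ANCOVA on the EDRC scale with the group contrast at T1, using robust or bootstrap standard errors. Fixing a single analysis matters more than which one is picked.
- Name one rank-based or permutation analysis as a sensitivity analysis.
- Limit log-transformation to strictly positive measures listed in advance, for example cortisol concentration and MEP amplitude.
- Reconcile Sample size (six raw measurements) with Statistical methods (five differences from baseline), and state the power of the analysis finally fixed, since 68 was derived for the six-measurement interaction.

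The cost is wording only. Removing the gate does not itself alter the stated 68 or 80, and the change can be made before unblinding. The downside is a slight loss of efficiency if EDRC is heavy-tailed, which the sensitivity analysis covers.

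### The T1 primary comparison of EDRC is tied to a repeated-measures ANOVA that by default uses only participants with every visit to one year, so observed T1 data can be discarded

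*Protocol article*

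**What the plan says.** Under Primary outcome measure, the protocol article sets the primary end-point as change in EDRC at T1. Under Participant timeline, T1 is the end of the six-week treatment, and T2 to T5 follow at one, three, six and twelve months.

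Under Statistical methods, EDRC enters a General Linear Model and "will be analyzed by means of repeated measures ANOVA with Group" (active or sham, each with usual treatment) as between-factor. The within-factor has five levels, the changes from T0 to each of T1, T2, T3, T4 and T5. No separate T1 analysis is named.

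Under Sample size, the calculation is "with an estimated f = 0.08" and a correlation of 0.80, and the number required for "6 measurements (T0 vs. T1 vs. T2 vs. T3 vs. T4 vs. T5) was 68 (i.e., 34 per group"). The article then states: "Considering a 15% dropout rate in the follow-ups, we will plan to recruit a total of 80 participants (i.e., 40 per group").

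**The concern.** The time point that defines success and the data that the model needs do not match. A classical repeated-measures ANOVA needs a complete vector of change scores for each participant. A participant who finishes treatment and completes the EDI-3 at T1, but misses a visit up to a year later, drops out of the model by default, and the observed T1 value goes too. The T1 comparison then depends on attendance long after T1.

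Two things are at stake. One is precision: T1 data already collected are not used. The other is validity: those who attend every visit may not represent those randomised. If poor early response makes later dropout more likely, and the loss differs between arms, the T1 difference among completers is distorted even though T1 was observed in everyone.

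**Working it through.** **1. Reproduce the plan's sample size.** Inputs from Sample size: f = 0.08, correlation ρ = 0.80, α = 0.05, power 0.80, k = 2 groups, m = 6 measurements. Formula for the within-between interaction, with sphericity assumed: λ = f²·N·m/(1−ρ), df1 = (k−1)(m−1), df2 = (N−k)(m−1).

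- At N = 68: λ = 0.0064 × 68 × 6 / 0.20 = 13.06, df = 5 and 330, power 0.8004.
- At N = 66: power 0.786. So 68 is the smallest even total, as stated.
- Dropout: 68/0.85 = 80, as stated.

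The 68 are therefore participants with all six measurements, and the plan expects 80 − 68 = 12 not to reach that. The article places this loss in the follow-ups. Twelve is an upper figure for discarded T1 values, because some may leave before T1.

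**2. Precision of the T1 contrast.** With ρ = 0.80, the SD of the T0–T1 change is √(2 × (1 − 0.80)) = 0.632 baseline SD.

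| Participants used at T1 | SE of group difference (baseline SD) |
|---|---|
| 80 (40 per arm) | 0.632 × √(2/40) = 0.141 |
| 68 (34 per arm) | 0.632 × √(2/34) = 0.153 |

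Ratio: √(80/68) = 1.085, about 8% larger.

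**3. Selection bias in the completers' T1 difference.** The documents give no dropout mechanism, so this step is illustrative. Assumptions: ρ = 0.80, 40 per arm, every T1 value observed, dropout only after T1 and more likely with poor T1 change (logistic slope 1.5 per SD of change), no true effect, t-test on the T1 change in completers.

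| Loss by arm | Bias (baseline SD) | Type I error |
|---|---|---|
| 15% and 15% | 0.00 | about 5% |
| 12.5% and 17.5% | 0.03 | about 5% |
| 10% and 20% | about 0.07 | about 7% |
| 7.5% and 22.5% | about 0.10 | about 10% |

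The type I error figures carry simulation error and move by about a percentage point between runs. Using all observed T1 data removes the bias in these scenarios.

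The direction depends on which arm loses more. Suppose a true T1 effect of 0.43 SD (an assumed value, not in the documents). Losing 7.5% of active and 22.5% of sham pulls the completers' estimate to about 0.33 SD, and power falls from 85% to 62%. With the arms reversed, the estimate rises to about 0.53 SD.

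**The case against.** The strongest reply is that the article nowhere says that incomplete participants are excluded. It names a model and is silent on missing data, and a condensed article commonly leaves that to the full protocol or analysis plan. Imputation followed by the same ANOVA would fit the text. This stands: exclusion is the default of the named method and not a written rule. It does not remove the point, which concerns the method that the article does fix. A one-year model is the only stated analysis for an end-of-treatment end-point, and the dropout arithmetic itself counts completers.

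A reader might infer three stronger things that the documents do not support.

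- *That the trial loses its planned power.* It does not. Inflation from 68 to 80 covers exactly this loss, and power at 68 completers is 0.8004. The loss in precision is relative to using all observed T1 data.
- *That the T1 result will be biased.* Bias needs response-related dropout that differs by arm. The article gives a single 15% rate, and participants, parents, treating staff and assessors are blinded. With equal loss by the same mechanism, the bias is nil and the type I error is about 5%. The threefold imbalance in the last row of the table is an extreme chosen for illustration.
- *That unchecked sphericity undermines the primary test.* When correlation decays at 0.90 to 0.97 per month, the uncorrected group by time interaction has a type I error of about 8%. The group main effect stays at 5%, and a T1 contrast from T1 data is unaffected. A Greenhouse-Geisser correction is routine detail that an analysis plan could supply, so this is secondary.

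**Conclusion.** The point holds in a limited form: a T1 end-point has been joined to a model that by default needs attendance to one year. On the plan's own figures, up to 12 of 80 observed T1 values could go unused, with a T1 standard error up to about 8% larger. This assumes that the 15% is overall loss, as 68/0.85 = 80 indicates, that all of it falls after T1, and that the default handling applies.

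The bias is conditional. It is zero under equal loss by the same mechanism and reaches about 0.07 to 0.10 SD, with type I error of about 7% to 10%, when the higher-loss arm loses two to three times as much as the other. How dropout will fall cannot be known in advance, and the exposure is avoidable at little cost. This is a change that should be made, not a flaw that invalidates the trial.

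**What to change.** For EDRC, replace the ANOVA with a likelihood-based mixed model for repeated measures. Include all randomised participants by allocated arm and every observed visit, with terms for baseline, group, visit and group by visit, and an unstructured covariance. Name a simpler structure in advance as a fallback if the model does not converge. State that the group contrast at T1 is the primary result. A baseline-adjusted ANCOVA at T1 is an acceptable alternative. Keep the complete-case ANOVA as a sensitivity analysis.

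The same model may be used for the other repeated outcomes for consistency. With unstructured covariance it also removes the sphericity assumption.

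The cost is a change of wording before unblinding and a little more analysis work in standard software. The covariance has more parameters: 5 × 6/2 = 15 for five post-baseline visits. Recruitment, visits and data collection are unchanged. For participants with no T1 value, the model still relies on missingness being explained by the observed data, so some sensitivity analysis remains worthwhile.

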In particular, this project has three different specific aims:*Specific Aim 1 “clinical efficacy”*: To evaluate the clinical efficacy of anodal/right cathodal tDCS to the PFC, coupled with a treatment-as-usual (TAU), in children and adolescents with AN in terms of: (1) changes in psychopathological measures, specifically changes in EDI-3 ED-specific (EDRC score) as primary outcome and changes in other psychopathological measures as secondary outcome; (2) changes in physiological measures, such as endogenous stress response system functioning, nutritional status, and BMI, as secondary outcome; (3) long-lasting effects until one year follow-up.*Specific Aim 2 “neurophysiological characterization at baseline”*: To characterize at baseline AN patients in terms of (1) intra-cortical inhibitory/excitatory motor circuits, and sensory-motor integration using pp-TMS; (2) cortical plasticity using rTMS; (3) cortical oscillations, reactivity, functional connectivity using TMS-EEG co-registration and to assess interhemispheric dynamics in terms of balance and inhibition.*Specific Aim 3 “association between efficacy and neurophysiological effect of tDCS treatment”*: To determine the neurophysiological patterns associated to behavioral changes induced by tDCS treatment, we will evaluate changes on plasticity and connectivity of the prefronto-motor networks, assessed by TMS-EEG, pp-TMS and rTMS, and their association to improvement.

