### Participant timeline

Baseline assessment (at time 0-T0) will be completed before the interventions are administered. Participants will undertake tDCS treatments (active or sham) plus a TAU for six weeks delivered for three times a week (18 session). Participants will be evaluated at the end of the treatment (at time 1-T1) and one-month later (at time 2-T2), three months later (at time 3-T3), six months later (at time 4-T4) and one year later (at time 5-T5). In the last follow-up, participants will be asked to indicate whether they believe they were receiving active or sham tDCS.

See Fig. 1 for details on the specific assessment of each visit.

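### The primary end-point is the EDRC change at T1, but the primary analysis is an ANOVA over five change scores to one year that names no deciding term and leaves the T1 group difference to unspecified Bonferroni post hoc tests

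*Protocol article*

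**What the plan says.** All the relevant text is in the Protocol article.

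- **Primary outcome measure** ties the end-point to one visit: "The primary end-point of the study is significant improvement on AN psychopathology at T1", measured by the change in the EDRC score. Participant timeline defines T1 as the end of the six-week treatment and T2 to T5 as 1, 3, 6 and 12 months later.
- **Objectives**, Aim 1, names EDRC as primary outcome in item 1 and lists persistence to one year separately as item 3.
- **Statistical methods** analyses the primary outcome by a repeated measures ANOVA that compares the two arms. Its repeated levels are five changes from baseline: "Follow-ups (T0-T1 vs T0-T2 vs T0-T3 vs T0-T4 vs T0-T5) as within-factor". On follow-up testing the section says: "Post hoc comparisons will be run by means of Bonferroni test". It does not say which term is the primary test, which comparisons are made post hoc, or how many there are.
- **Sample size** starts from this: "Assuming a correlation of 0.80 in the primary outcome measure (EDRC score of EDI-3 questionnaire) with an estimated f = 0.08". The design there is 2 groups by 6 measurements, T0 to T5, giving 68 participants, raised to 80 for 15% dropout.

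**The concern.** The end-point and the model answer different questions. When the levels of the within-factor are changes from baseline, the Group term compares the arms on the mean of the five changes, so T1 carries one fifth of the weight. The Group by Follow-ups term tests whether the arm difference is the same at every visit. It is null by construction when a benefit is present at T1 and fully kept.

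Three consequences follow. A benefit at T1 that fades can leave the Group term non-significant. A benefit that appears only months later can make the Group term significant and be reported as success on an end-point fixed at T1. And with two omnibus terms and an undefined set of post hoc tests available, the deciding test could be chosen after the data are seen, so the 5% error rate is not pinned down.

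**Working it through.** **Inputs from the document.** f = 0.08, correlation 0.80, alpha 0.05, 2 groups, 6 measurements, N = 68 (34 per arm), 80 recruited (40 per arm).

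**Assumptions.** The document gives no EDRC difference or SD, so SD is set to 1 at each visit, with correlation 0.80 between every pair of visits (sphericity holds).

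**1. The plan's own figure.** For the within-between interaction, λ = f²·N·m/(1 − ρ) = 0.0064 × 68 × 6 / 0.20 = 13.06, with df 5 and 330. Power is 0.800, so N = 68 reproduces, and 68/0.85 = 80. The figure therefore belongs to an omnibus test over six visits including T0. The Group term of that six-visit model would need N = 1024.

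**2. From f to a group difference.** With d_j the arm difference at visit j (zero at T0), f² = mean[(d_j − d̄)²]/4 over the six visits. The multipliers below are for T0 to T5.
- Sustained (0,1,1,1,1,1), T1 only (0,1,0,0,0,0) and linear waning (0,1,0.75,0.5,0.25,0): the variance of the multipliers is 5/36 in each, so d = 2 × 0.08/√(5/36) = 0.43 SD at T1.
- Late, T3 to T5 only (0,0,0,1,1,1): the variance is 1/4, so d = 2 × 0.08/0.5 = 0.32 SD, and zero at T1.

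**3. Variances.**
- One change score: 2(1 − ρ) = 0.40.
- Mean of five changes: (1 − ρ) + (1 − ρ)/5 = 0.24.
- Interaction error: 1 − ρ = 0.20.
- T1 adjusted for baseline: 1 − ρ² = 0.36.

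**4. Noncentrality, n per arm.**
- Group term: mean change difference / √(0.24 × 2/n). Sustained at n = 34: 0.429/0.1188 = 3.61. T1 only: 0.0859/0.1188 = 0.72. Waning: 0.2147/0.1188 = 1.81. Late: 0.192/0.1188 = 1.62.
- Interaction, df 4 and 264: λ = 2n·Σ(c_j − c̄)²/(4 × 0.20), where c_j is the arm difference in change at visit j. This gives 0, 12.5, 9.8 and 10.4 in the same order.
- T1 change score: 0.429/√(0.40 × 2/34) = 2.80.

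**5. Power at 34 per arm.**

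| Pattern (f = 0.08) | Group term | Interaction | T1 test at 0.05 |
|---|---|---|---|
| Sustained | 95% | 5% (its null holds) | 79% |
| T1 only | 11% | 81% | 79% |
| Linear waning to zero at T5 | 43% | 70% | 79% |
| T3 to T5 only | 36% | 73% | 5% (no T1 effect) |

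With 40 per arm the T1 test has 85% in the first three rows. Adjusted for baseline EDRC it has 83% with 34 per arm.

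**6. Cost of reaching T1 only post hoc.** The number of comparisons is not stated. Power of the T1 change-score test for 0.43 SD, by assumed family size:

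| Comparisons | Alpha each | 34 per arm | 40 per arm |
|---|---|---|---|
| 1 | 0.05 | 79% | 85% |
| 2 | 0.025 | 69% | 77% |
| 5 | 0.01 | 56% | 65% |
| 10 | 0.005 | 46% | 56% |

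**7. Type I error if either omnibus term counts.** Under sphericity the two tests are independent, so 1 − 0.95² = 9.75%.

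**8. Sized model against planned model.** In the six-visit model of Sample size, a sustained effect gives an interaction with 80% power. Statistical methods moves T0 into the change scores and leaves five levels, where the same effect gives no interaction (5%).

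**The case against.** A reader might infer that the plan contains no test of the T1 difference at all. The text does not support that. The T0 to T1 change is one level of the within-factor, so active versus sham at T1 can be among the post hoc comparisons. The defect is that this comparison is neither specified nor designated as primary. Nor does the whole ANOVA average over visits: only the Group term does.

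A reader might also infer that the ANOVA would usually overlook a T1 benefit. It would not. In each of the three T1-benefit patterns one of the two terms has good power, and the chance that at least one is significant is 1 − (0.055 × 0.95) = 95% for sustained, 1 − (0.89 × 0.186) = 83% for T1 only, and 1 − (0.571 × 0.303) = 83% for waning. This stands, but it defends the plan only if either term may count. That costs about 9.75% type I error, and the late pattern with no T1 effect would then count as success as well.

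Nor is the trial too small for T1. The 15% dropout is placed in the follow-ups and T1 is the first visit after baseline, so between 34 and 40 per arm may contribute. A single T1 test then has 79% to 85% power under the stated assumptions.

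Finally, an analysis plan that is not shown may define the contrasts. Such detail can properly be left to it. But the protocol itself states both a T1 end-point and the analysis of that end-point, and the two do not match.

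**Conclusion.** The mismatch is real and concerns the test that decides the trial, so it must be fixed. The planned analysis names no deciding term, neither omnibus term isolates T1, and T1 is left to post hoc comparisons of unstated number. The two omnibus terms give opposite answers for a sustained effect (95% against 5%) and for a T1-only effect (11% against 81%), so the conclusion depends on which one is read. An effect of 0.32 SD confined to T3 to T5 gives about a 36% chance of a significant Group term with no effect at T1.

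These sizes rest on equal SDs, correlation 0.80 between all visits, f = 0.08 and the four patterns chosen. The 56% (65% with 40 per arm) rests further on an assumed five comparisons. That the model does not isolate the end-point depends on none of these assumptions.

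**What to change.** In Statistical methods, name the active-versus-sham difference in EDRC change from T0 to T1 as the single primary test, two-sided alpha 0.05, with no Bonferroni correction on that contrast. It can be a prespecified contrast in the longitudinal model or a separate T1 comparison. Adjustment for baseline EDRC is preferable (about 83% against 79% power at 34 per arm) but is not needed to cure the mismatch. Make the T2 to T5 contrasts, the averaged Group effect and the interaction secondary, and list which post hoc comparisons belong to the Bonferroni family. In Sample size, add the power for the T1 contrast, with the EDRC difference and SD assumed.

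The cost is wording only. No patients, visits or data are added, and the longitudinal analyses are kept.
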